#### Body Composition

Using a digital scale and a stadiometer, weight and height will be measured (Tanita MC-780U [Tanita Corporation] and Seca 222 [Seca, GmbH & Co], respectively). For weight, the participant must be without shoes and with as little clothing as possible, while for height, they must be in a standing position, obtaining the value at the end of a normal inspiration. Both measurements will be taken in duplicate using the average to calculate the BMI.

Waist circumference will be determined as mentioned subsequently. On the right side of the body, a mark will be made on the skin at the height of the last rib, then a mark will be made on the skin at the top of the iliac crest. The distance between both marks will be calculated, and, at the midpoint, a final mark will be made. The same procedure will be performed on the left side. Using a tape measure, which must be at the height of both end marks on each side, the value will be determined at the end of a normal expiration. For the analyses, the average of 2 measurements will be used.

The percentage of adipose and muscle tissue will be calculated from the average of 2 evaluations performed in a state of rest and fasting, with the minimum amount of clothing and after urinating and resting for 15 minutes, using tetrapolar electrical bioimpedance (Tanita MC-780U). It will be complemented by the measurement of skinfolds, body perimeters, and bone diameters [32].

### Covariables

Before the start of the intervention, sociodemographic variables will be collected through a questionnaire, including questions on age, sex, career, means of transport, geographic area of residence, screen time, and socioeconomic level of the participants.

### Ethical Considerations

This protocol was approved by the scientific ethics committee of the Universidad Autónoma de Chile as well as the informed consent document (Scientific Ethics Committee CECP 28-25), which participants must sign at the beginning of the study. They will receive a copy of the signed consent form and will be given the opportunity to ask questions related to the study. The procedures will be executed in accordance with the Declaration of Helsinki. In addition, this study has been registered on ClinicalTrials.gov (NCT06580769). Participants may withdraw from the study at any time without having to justify their decision. To safeguard participant privacy and the integrity of the collected data, the following measures will be implemented: the collected data are confidential and will be stored in locked files accessible only to the principal investigator. The data will be anonymized. Only anonymized data will be used for publications or presentations.

### Statistical Analysis

The normality of the data will be checked through the Kolmogorov-Smirnov test, which will indicate the steps to be taken in relation to the comparison tests. Once the pretest tests have been performed, comparison analyses will be performed between groups (2-tailed Student *t* test or Mann-Whitney *U* test) to check the homogeneity of the groups. At the conclusion of the final evaluations of the study, intragroup differences will be analyzed using a statistical test of repeated measures (Student *t* test for related samples or Wilcoxon signed-rank test), along with the intergroup differences (Student *t* test or Mann-Whitney *U* test).

Cohen *d* will be used to determine the effect size on variables in which significant differences are found, using the following scale: 0.2 or greater=small, 0.5 or greater=moderate, and 0.8 or greater=large [33]. In addition, regression analyses will be performed incorporating the covariates. The simple imputation method will be used for all analyses [34], keeping the participants in the group to which they were assigned (intervention or control) regardless of the sessions they attended [35]. In valid cases, analyses will be performed to determine sensitivity [36]. For all tests, statistical significance will be set to *P*<.05. The data will be analyzed using SPSS statistics (version 29; IBM Corp).

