### Sample Size Calculation

On the basis of what was proposed for the design of the RCTs [27], the number of participants will be calculated. Taking 2 RCTs that aimed to increase physical activity levels through walking [18,19] as reference, the sample will be calculated considering an absolute difference of 3% (α error of .05 and statistical power of .80) between the intervention group and the control group in the mean percentage of cardiorespiratory endurance (SD 5), giving a required sample of 99 participants for each group (intervention and control).

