### Measuring Health Indicators

#### Cardiorespiratory Fitness

This indicator will be measured through the 20-m shuttle run test [31]. Participants must run between 2 lines separated by 20 m. The speed at which they must move is indicated by a sound emitted by a recorded tape. The participant begins at a speed of 8.5 km/h, which increases by 0.5 km/h every minute. When a participant being evaluated fails to reach the lines twice in a row, along with the sound, or when they are unable to continue running the test, the evaluation is completed, and the minute reached is recorded. According to the proposal, the maximum oxygen consumption is estimated [31].

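### A Kolmogorov-Smirnov pre-test decides outcome by outcome between a mean comparison and a rank test, so the effect being tested is not fixed, although the trial is sized on a mean difference

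*Protocol article*

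**What the plan says.** **Statistical Analysis.** A Kolmogorov-Smirnov test is run first, and its result governs the comparisons: "which will indicate the steps to be taken in relation to the comparison tests". The baseline between-group comparison is a "2-tailed Student *t* test or Mann-Whitney *U* test". The same pair is named for the final between-group comparison, and paired t or Wilcoxon signed-rank for change within a group. No outcome is given a fixed test. Cohen d is planned for outcomes that reach significance, without regard to which test produced the P value. Regression with the covariates is added, but has no stated primary role. On the level, the section says: "For all tests, statistical significance will be set to *P*<.05".

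**Sample Size Calculation.** The trial is sized on an absolute difference of 3 with SD 5 in mean cardiorespiratory endurance, with "α error of .05 and statistical power of .80", giving 99 per group.

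**Cardiorespiratory Fitness.** The shuttle run starts at 8.5 km/h and speeds up by 0.5 km/h each minute. When the participant stops, "the evaluation is completed, and the minute reached is recorded". Maximum oxygen consumption is then estimated by a published method whose equation the article does not give.

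**The concern.** The three sections do not fit together. The sizing is for a mean difference, but the analysis rule can replace the mean comparison with a rank comparison, depending on how the trial's own data look. Mann-Whitney gives no estimate of the planned mean difference. A rank-based P value could then stand beside a mean-based Cohen d for the same outcome. Different outcomes, or the baseline and final values of one outcome, could also end up under different tests.

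The shuttle run makes the switch more than theoretical. A score recorded by the minute is coarse, and Kolmogorov-Smirnov compares a smooth normal curve with an empirical distribution that rises in steps. Rounding alone can therefore count as non-normality. At stake is whether the headline result for cardiorespiratory fitness is an effect on the planned scale.

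**Working it through.** **1. The plan's own figure.** With n per group = 2(z₀.₉₇₅ + z₀.₈₀)² SD²/Δ² and z-sum 2.8016:
- Δ = 3, SD = 5: 2 × 7.849 × 25/9 = 43.6, so 44 per group (45 with the t distribution).
- Δ = 2, SD = 5: 2 × 7.849 × 25/4 = 98.1, so 99 per group.

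The stated 99 does not follow from a difference of 3, but does follow from a difference of 2. That is a separate matter. Here it means that both standardised effects, 3/5 = 0.6 and 2/5 = 0.4, have to be examined. Either way the target is a mean difference.

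**2. How often ties alone trigger rejection.** The article gives no SD in minutes, no exact rounding rule and no version of the Kolmogorov-Smirnov test, so these are assumptions shown as ranges. Underlying endurance was exactly normal (mean between 5 and 6 min) and rounded down; n=99; 5,000 samples per row; mean and SD estimated from the sample. Critical values at the 5% level were 0.0891 (Lilliefors, simulated) and 0.1347 (uncorrected).

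| SD (min) | Whole minutes, Lilliefors | Whole minutes, uncorrected | Half minutes, Lilliefors |
|---|---|---|---|
| 1 | 100% | 100% | 99.9% |
| 1.5 | 100% | 89% | 80% |
| 2 | 99.9% | 35% | 51% |
| 2.5 | 96% | 12% | 34% |
| 3 | 81% | 5% | 25% |
| 4 | 52% | 1% | 16% |

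Pooling both arms (n=198) raises the uncorrected whole-minute rate at SD 2 from 35% to 99%. The branch taken thus depends on rounding, on the version of the test and on which data are fed to it.

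**3. What follows from the switch.** Each simulated trial had 99 per arm and whole-minute scores. Lilliefors was run in each arm, then either the t test or the tie-corrected Mann-Whitney was applied (two-sided 5%; 4,000 trials per setting; SD 1 to 2.5 min). The two-sided level is stated for the baseline comparison and assumed for the final one. The procedure went to Mann-Whitney in 99.7-100% of trials.

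| Standardised effect | Fixed t test | With the gate |
|---|---|---|
| 0 (type I error) | 4.6-5.0% | 4.6-5.2% |
| 0.4 (power) | 77-79% | 75-77% |
| 0.6 (power) | 97.7-98.8% | 97.5-98.6% |

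Setting by setting, the gate lost 0.2 to 2.5 points of power. The fixed t test needed no protection from the rounding.

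**4. What baseline adjustment would add.** Adjusting for a baseline value with pre-post correlation ρ divides the residual SD by √(1/(1 − ρ²)). Without rounding, approximate power at 99 per arm is Φ(d/√(1 − ρ²) × √(99/2) − 1.96):
- d = 0.4, ρ = 0: 0.4 × 7.036 = 2.814, power 80%.
- d = 0.4, ρ = 0.5: 0.4/0.866 × 7.036 = 3.250, power 90%.
- d = 0.4, ρ = 0.7: 0.4/0.714 × 7.036 = 3.941, power 98%.

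With whole-minute rounding, simulation gives about 79% unadjusted and about 96% adjusted at ρ = 0.7. The correlation is an assumption; the article gives none.

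**The case against.** The strongest reply is that the gate does almost no damage to error rates. Step 3 confirms this. A reader who sees 95-100% rejection might infer inflated type I error or a serious loss of power; neither is shown.

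The tie mechanism is also conditional. The article does not say that only whole completed minutes count, and the oxygen equation is not shown. If that equation includes a finely measured covariate, some ties break and rejection becomes less frequent. With the uncorrected test and SD 3 min, only 5% of samples reject. A reader might infer that the fitness outcome is bound to switch to a rank test; the document does not establish that. Nor does it define the percentage endurance measure used for sizing as the shuttle result, although the shuttle run is the only cardiorespiratory measure described.

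Three further inferences fail or need limiting:
- That outcomes could not be compared on one scale: Cohen d is planned for significant outcomes and is such a scale.
- That the rank test is worse because it cannot adjust for baseline: the planned t test does not adjust either.
- That the analysis is left to free choice after the data are seen: a rule with named alternatives is set in advance. Moreover, if the treatment effect is a pure location shift, both tests share the same null hypothesis.

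What stands is that the rule lets the data decide which kind of effect is tested, and that it brings no benefit at this sample size. The planned regression does not repair this: it has no primary role, and the listed covariates are sociodemographic and do not include baseline outcome values.

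**Conclusion.** The point holds as a flaw in a stated rule, and changing it is advisable. The pre-test leaves open, for each outcome, whether a mean or a rank comparison is made, in a trial that is sized on a mean difference and reports a mean-based effect size.

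The size is modest. In whole-minute simulations with normal underlying data, type I error was near 5% with or without the gate, and the power cost was about 0 to 2.5 points. The chance that rounding alone triggers the switch runs from about 5% (uncorrected test, SD 3 min) to 100% (Lilliefors, SD 1.5 min or less). It rests on whole-minute scoring and on an oxygen estimate that depends on the stage alone.

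**What to change.** In the Statistical Analysis section:
- Remove the normality test as a gate.
- For all continuous outcomes, pre-specify one between-group linear model of the final value on group and the baseline value of the same outcome, with heteroscedasticity-robust standard errors. Report the adjusted mean difference with its confidence interval.
- Inspect residuals, and give a rank-based or bootstrap analysis as a labelled sensitivity analysis only.

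**Cost.** Only analysis wording changes. The baseline values are already collected and the 99 per group need not change on this account. A strongly skewed secondary outcome, such as a skinfold, may lose a little power; the sensitivity analysis covers that case. Most of the statistical gain comes from the baseline adjustment, and dropping the gate serves mainly to fix the effect measure in advance.

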### Participants

Participants will be gathered from the Universidad Autónoma de Chile across the campuses located in the cities of Santiago, Talca, and Temuco. Information about the intervention will be disseminated through institutional email, social networks, and informative posters. The following inclusion criteria will be considered: (1) be a university student with active enrollment at the Universidad Autónoma de Chile, (2) aged between 18 and 25 years, (3) have medical consent that authorizes the regular practice of physical activity, and (4) sign an informed consent form to participate in the study. The exclusion criteria will be as follows: (1) having a physical or mental impediment that prevents or limits the performance of physical activity and (2) belonging to special groups, such as professional athletes or pregnant women. The evaluations at the beginning and end of the study will be performed at the university’s facilities using the equipment available at each of the respective campuses (Santiago, Talca, and Temuco).

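### No stated between-group estimate uses the baseline outcome measured on every participant, and within-group tests are listed without saying that they do not test the intervention

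*Protocol article*

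**What the plan says.** The Statistical Analysis section of the protocol article names four steps for the outcomes.

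- **Baseline.** After the pretest, "comparison analyses will be performed between groups" ("2-tailed Student *t* test or Mann-Whitney *U* test") to check that the groups are homogeneous.
- **Within each arm.** "At the conclusion of the final evaluations of the study, intragroup differences will be analyzed using a statistical test of repeated measures": a paired t test or Wilcoxon signed-rank test.
- **Between arms.** In the same sentence, intergroup differences are tested by a t or Mann-Whitney test. The text does not say whether final values or changes are compared. Final values are the natural reading, since change scores are not mentioned.
- **Regression.** "In addition, regression analyses will be performed incorporating the covariates". The Covariables section describes these as sociodemographic variables from a questionnaire, "including questions on age, sex, career, means of transport, geographic area of residence, screen time, and socioeconomic level of the participants". No baseline outcome value is listed.

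The same section applies a threshold of P<.05 to all tests. It gives Cohen d for variables with significant differences, without limiting this to differences between groups. The Abstract and the section on adherence criteria confirm that both arms are assessed at the beginning and the end.

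**The concern.** Two separate things are at stake.

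**Precision.** Fitness, grip strength and body composition can be expected to differ more between people than they change within a person over 14 weeks. If so, the baseline value explains a good part of the variation in the final value. A comparison that ignores it has a wider confidence interval than necessary and leaves any chance baseline imbalance in the estimate.

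**Interpretation.** A paired test within one arm measures change over time, whatever its cause. Change shared by both arms is plausible here: controls wear the same tracker and submit weekly logs, the Discussion itself acknowledges reactivity to monitoring, and the shuttle run is performed twice. A significant change in one arm beside a non-significant change in the other does not show that the arms differ. The plan lists the paired tests alongside the intergroup test, does not say which one carries the conclusion, and would attach Cohen d to any significant result.

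**Working it through.** **Inputs.** From Sample Size Calculation: "the sample will be calculated considering an absolute difference of 3" percent, SD 5, "α error of .05 and statistical power of .80", 99 per group. Two-sided testing is assumed there, in line with the two-tailed t test named in Statistical Analysis. The pre-post correlation r is not given anywhere; 0.5 to 0.85 is assumed, with 0.3 as a low value. Equal SDs at both time points are also assumed.

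**1. The plan's own figure.** n per group = 2 × 5² × (1.960 + 0.842)² / 3² = 43.6, so 44, not 99. A difference of 2 with SD 5 gives 98.1, so 99. This mismatch is a separate matter. What counts here is that at 99 per group the standard error of an unadjusted comparison is 5 × √(2/99) = 0.711. Power for a difference of 3 is then Φ(3/0.711 − 1.960) = 0.988.

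**2. Gain from baseline adjustment.** The smallest difference detectable with 80% power by the unadjusted comparison is 0.711 × 2.802 = 1.99. ANCOVA multiplies the standard error by √(1 − r²), and 99 per group then performs like 99/(1 − r²).

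| r (assumed) | SE ratio | SE reduction | Equivalent n per group | Detectable difference |
|---|---|---|---|---|
| 0.3 | 0.954 | 5% | 109 | 1.90 |
| 0.5 | 0.866 | 13% | 132 | 1.72 |
| 0.7 | 0.714 | 29% | 194 | 1.42 |
| 0.85 | 0.527 | 47% | 357 | 1.05 |

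**3. If change scores were meant.** Their SD is 5 × √(2(1 − r)). Power for a difference of 1.99 at 99 per group:

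| r (assumed) | Final values | Change scores | ANCOVA |
|---|---|---|---|
| 0.3 | 0.80 | 0.66 | 0.84 |
| 0.5 | 0.80 | 0.80 | 0.90 |
| 0.7 | 0.80 | 0.95 | 0.975 |
| 0.8 | 0.80 | 0.993 | 0.997 |

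Change scores do worse than final values below r = 0.5. ANCOVA has the highest power in every row.

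**4. Separate paired tests when there is no treatment effect.** Let both arms truly change by the same amount, and let p be the probability that one arm's paired test is significant (noncentral t, n = 99, SD 5). The arms are independent, so P(exactly one significant) = 2p(1 − p), and P(only the intervention arm significant) = p(1 − p).

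| r | Shared change | p | Exactly one arm | Intervention arm only |
|---|---|---|---|---|
| any | 0 | 0.050 | 0.095 | 0.048 |
| 0.5 | 0.5 | 0.166 | 0.278 | 0.139 |
| 0.5 | 1.0 | 0.504 | 0.500 | 0.250 |
| 0.7 | 0.75 | 0.479 | 0.499 | 0.250 |
| 0.7 | 1.5 | 0.968 | 0.061 | 0.031 |

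The maximum of 2p(1 − p) is 0.50, at p = 0.5. The probability falls again once the shared change is large enough for both arms to be significant almost every time.

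**The case against.** The strongest reply is that a valid test is already planned. With randomised groups, the unadjusted intergroup comparison keeps its type I error, and for the protocol's own difference of 3 it has power of about 0.99. Nothing in the text says that efficacy will be judged by contrasting the two within-group P values. The article is condensed, the covariate list need not be exhaustive, and exact model terms may be left to an analysis plan that is not shown. The baseline homogeneity test is uninformative, but no decision is attached to it.

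Most of this stands, and it rules out several stronger readings that a reader might draw:

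- **That the main comparison is invalid.** It is not; its cost is precision.
- **That most of the available precision is lost.** The share of variance removed by adjustment is r², which exceeds one half only for r above about 0.71, and the documents give no r.
- **That there is a 50% risk of a false claim of benefit.** The value 0.50 is the ceiling of 2p(1 − p), and only half of those cases point towards the intervention.
- **That campus equipment distorts the comparison.** The Participants section speaks of "using the equipment available at each of the respective campuses (Santiago, Talca, and Temuco"), but the measurement sections name specific device models. No difference between campuses is documented.

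What the reply does not remove is that the article does fix the tests. None of the between-group analyses it names is said to use the baseline outcome, and the regression is tied to covariates defined as sociodemographic. Sex is among them, which recovers some precision but does not replace the baseline value. The role of the paired tests also remains open.

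**Conclusion.** The point holds as a should-fix and an essentially free improvement. As stated, the plan uses baseline outcomes for a homogeneity check and for paired tests, but in no explicit between-group estimate. The precision forgone is a 13% to 47% larger reduction in standard error than the plan obtains, if r lies between 0.5 and 0.85, and about 5% if r is only 0.3. These figures are relative to an unadjusted comparison of final values. The gain matters for differences well below 3 units and for grip strength and body composition, for which the sample size section gives no calculation; it is not needed to reach the planned power for 3 units.

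The within-group tests carry a real risk of misreading, because one P threshold covers all tests and Cohen d follows any significant difference. Discordant paired results with no treatment effect have probability 0.095 when neither arm changes and 0.50 at worst. Whether they would be misread depends on how the results are reported, which the article leaves open.

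**What to change.** Rewrite the analysis paragraph as follows.

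- **Main analysis.** For each outcome, fit a linear model of the final value on group and the baseline value of that same outcome. Report the adjusted mean difference with its 95% CI. Sex and campus may be added as prespecified covariates. State that this contrast carries the conclusion about the intervention.
- **Within-group changes.** Report them descriptively, without P values or efficacy claims.
- **Effect size.** Limit Cohen d to the between-group contrast.
- **Baseline.** Replace the homogeneity tests with a descriptive table by group.
- **Covariate regression.** Keep the regression on the sociodemographic covariates as a supportive analysis.

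The cost is rewording one paragraph. The model is available in the SPSS version already planned, and it needs no new data or visits. The change should be made before outcome data are examined.

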## Discussion

### Anticipated Findings

Considering that there is currently a high number of inactive adults [7] and that sedentary behaviors predominate in university students’ daily lives due to academic demands—which is associated with damage to their health [13]—it is necessary to implement strategies to help address this problem. Interventions based on wearable technologies have shown increases in daily step counts and, to a lesser extent, activity intensity, with small to moderate effects and heterogeneity between populations [16,18,26]. These findings support the use of goals and objective monitoring as key components.

One option that has proven to be effective, low cost, and easy to implement is physical activity through walking, which is monitored by daily step trackers. However, most studies implementing this strategy have generated evidence by monitoring physical activity for 7 days on average [37], which could cause the reported results to be biased because participants could change their physical activity behaviors because they are aware that they are being evaluated [21]. This reinforces the need for research with longer follow-up periods that allow for a more detailed analysis of the relationship between daily steps and health indicators. In the university population, recent studies have shown that programs of 8 to 12 weeks supported by mobile apps and messaging can lead to significant increases in daily steps [21,22,25,27]. On the basis of this evidence, this protocol proposes a duration of 14 weeks, with individualized goals and weekly feedback, with the aim of achieving more sustained effects than those observed in interventions of shorter duration.

The choice of a long period is based on the need to assess the sustainability of change, given that recent reviews suggest that initial increases may decrease over time [5,20]. Likewise, setting explicit daily goals has been associated with higher levels of compliance, and more recent proposals even propose hourly objectives as a tactic to achieve the daily goal [17,29].

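### Cohen d is planned only for variables with significant differences, so reported effect sizes are selected by P value and overstated where true effects are small

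*Protocol article*

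**What the plan says.** The Statistical Analysis section of the protocol article first lists the tests. Within groups these are the paired t test or the Wilcoxon signed-rank test. Between groups they are the t test or the Mann-Whitney U test. It then plans Cohen d "to determine the effect size on variables in which significant differences are found", graded as "0.2 or greater=small, 0.5 or greater=moderate, and 0.8 or greater=large", with significance set at P<.05 for all tests.

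The same section adds regression analyses with the covariates. It attaches no significance condition to them, and it does not say which outcomes they cover or which quantities will be reported. The article nowhere provides for a standardised effect or a confidence interval for an outcome that misses significance.

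Sample Size Calculation supplies the other inputs: "considering an absolute difference of 3" percent with SD 5, "α error of .05 and statistical power of .80", and "giving a required sample of 99 participants for each group".

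**The concern.** An effect size that is calculated only after a significant test comes from the upper part of its sampling distribution. When the true effect is modest relative to the standard error, the results that pass the filter are the ones that chance pushed upward, so the reported values are too large on average. Outcomes that fail the filter have no planned effect size, and without one and its interval a reader cannot tell an effect near zero from an imprecise estimate.

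The trial measures several outcomes: shuttle-run fitness, grip strength, BMI, waist circumference, and adipose and muscle percentage. Only cardiorespiratory endurance has a sample size rationale, so the others may have smaller true effects. The reported d values would then be a selected set, and would mislead anyone who used them to judge the programme or to combine it with other studies.

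**Working it through.** **Inputs.** From Sample Size Calculation: 99 per group, difference 3, SD 5, alpha 0.05, power 0.80. From Statistical Analysis: threshold P<.05 and the 0.2/0.5/0.8 scale. The section says "2-tailed Student" for the baseline comparison; I assume that the final between-group test is two-sided too.

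**The plan's own figure.** The usual formula for two means gives n = 2 × (1.960 + 0.842)² × 5² / 3² = 2 × 7.849 × 25 / 9 = 43.6, that is 44 per group and not 99. The stated 99 matches a standardised difference of 0.4 (a difference of 2 with SD 5, or of 3 with SD 7.5). That is a separate matter. Here I take 99 per group as the trial's size and 3/5 = 0.6 as its planning effect.

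**Step 1: smallest reportable d, between groups.** With t(0.975; 196 df) = 1.972, the smallest significant |d| is 1.972 × √(2/99) = 1.972 × 0.1421 = 0.280. An observed d from 0.20 to 0.28 is small on the plan's scale but cannot be reported.

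**Step 2: smallest reportable d, within a group.** For a paired t test with 99 pairs, t(0.975; 98 df) = 1.984 and the floor is 1.984 / √99 = 0.199. This is d scaled to the SD of the change.

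**Step 3: average reported |d| between groups.** One million simulated two-sample t tests per scenario, 99 per group, averaging |d| over runs with two-sided P<.05:

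| True d | Trials with no d reported | Mean reported \|d\| | Ratio to truth |
|---|---|---|---|
| 0 | 95% | 0.34 | – |
| 0.1 | 89% | 0.35 | 3.5 |
| 0.2 | 71% | 0.37 | 1.85 |
| 0.3 | 44% | 0.40 | 1.34 |
| 0.4 | 20% | 0.45 | 1.13 |
| 0.5 | 6% | 0.52 | 1.04 |
| 0.6 | 1% | 0.61 | 1.01 |

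At true d = 0.1 the signed mean is 0.33. It is lower than 0.35 because some significant results point the wrong way.

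**Step 4: check by hand at true d = 0.2.** Take the estimate as normal with SE 0.1421. The cut-off lies (0.2803 − 0.2) / 0.1421 = 0.565 SE above the truth. The chance of exceeding it is 0.286 and the normal density there is 0.340. The mean above the cut-off is 0.2 + 0.1421 × 0.340 / 0.286 = 0.369, in agreement with the simulation.

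**Step 5: without the filter.** If d is calculated in every run, its mean is 0.20 at true 0.2 and 0.40 at true 0.4. The excess in the table comes from the selection alone.

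**The case against.** The strongest reply is that the problem vanishes at the only effect that the protocol plans for. At 0.6 the inflation is 1% and about 99% of trials would report a d. This stands, and it limits the point to outcomes with smaller true effects.

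Second, the section states when Cohen d is calculated; it does not say that other results will be withheld. Group means and SDs may be published, the regressions are not tied to significance, and the article commits to CONSORT reporting. A reader might infer that non-significant outcomes get no estimate or interval at all. The text does not go that far: it removes the planned effect size, and is silent on the rest. Still, an unspecified regression and a general reporting commitment do not cancel an explicit filter on the one effect measure that the plan names.

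Three other stronger readings also fail:

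- *Every reported d is at least 0.28.* That floor belongs to the two-sample t test. The paired floor is about 0.20, and 0.28 is not exact for Mann-Whitney.
- *The protocol itself expects small to moderate effects.* The Anticipated Findings phrase "with small to moderate effects and heterogeneity between populations" describes what earlier wearable interventions showed for step counts and activity intensity. It is not a forecast for this trial's fitness, strength and body composition outcomes.
- *Cohen d is applied where means and SDs have been ruled out.* The normality check chooses the comparison test. The section does not call means and SDs unsuitable.

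**Conclusion.** The point holds within limits. The significance condition is a written rule, not a detail that a condensed article leaves out, and it selects reported effect sizes by P value. For between-group t tests at 99 per arm it overstates |d| on average by about 85% at a true effect of 0.2, 34% at 0.3 and 13% at 0.4. From 0.5 upward the overstatement is at most about 4%.

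These figures assume 99 analysed per arm, normal outcomes with equal SDs, an unadjusted two-sided test and one comparison at a time. The documents do not give true effects for the individual outcomes, so the whole range is shown and no single figure should be read as the expected bias. No hypothesis test, analysis population or sample size is affected. This is a flaw in what will be reported. It should be corrected, but it does not threaten the trial's validity.

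**What to change.** In Statistical Analysis, delete the condition that ties Cohen d to a significant result. State instead that for every outcome, whatever its P value, the report will give the between-arm difference in the outcome's own units with a 95% CI, and the standardised difference with a 95% CI. Use the small, moderate and large labels only beside the interval.

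The cost is a fuller results table. The change needs no extra participants, measurements or procedures, and can be made at any time before the analysis.
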